### Data collection (process evaluation)

The process evaluation will be based on realist evaluation [48, 49]. The key question that a realist evaluation seeks to answer is: What works for whom under which circumstances? The questions are answered through the test of context, mechanisms and outcome (CMO) configurations, i.e., exploring in which Contexts an interventions Mechanisms are triggered, to bring about the intended Outcomes [48]. Although realist evaluation has received limited attention in the training literature, recent frameworks have argued that realist evaluation may be used to understand the impact of training interventions to improve employee mental health integrating a training transfer perspective [50, 51]. For example, it has been found that important mechanisms for learning and intention to transfer (intermediate outcomes) are the design and format of the training, as well as participants’ satisfaction with the training [38]. Key contextual factors that may influence how participants react to training are factors such as readiness for change, support from senior management and the extent to which participating managers feel the training fits in their daily work context [50]. Thus, contextual factors involve both the organizational context and individual characteristics [50]. Our outcomes are listed below.

Nielsen and Shepherd [50] suggested a chain of effects, with intermediate outcomes: The extent to which participants feel they have acquired new learning (first proximal outcome) and intend to transfer this learning (second proximal outcome) will result in transfer attempts to translate the acquired learning (third proximal outcome) into new leadership behaviors (fourth proximal outcome), which potentially should lead to improvements in employees’ mental health and wellbeing (distal outcomes). At each identified step, contextual factors may influence the extent to which the outcomes are brought about by the mechanisms intended to facilitate the outcome and these will be captured by both the quantitative and qualitative process evaluation.

The current process evaluation was inspired by the Integrated Training Transfer and Effectiveness Model (ITTEM) framework developed by Nielsen and Shepherd [50] that integrates training transfer and training effectiveness. The ITTEM framework suggests that pre-and post-training contextual factors at both the individual and organizational levels influence the extent to which training transfer mechanisms are triggered. Thus, an advantage of this model is that it links the concept of transfer to outcomes and training effectiveness (i.e., whether training is actually transferred to and integrated in new practices at the workplace as well as if the relevant training outcomes are achieved).

The process evaluation will use both quantitative and qualitative data to test the CMOs of the study, which are outlined below:• If managers are highly motivated for training and have volunteered to participate in training, then they are more likely to participate in all training modules and as a result, managers will report learning as an outcome of the training (proximal outcome for managers).• If managers are confident about managing the psychosocial work environment, then they will engage in more transfer attempts and as a result they will be likely to report improvements in staff-care (intermediate outcome) with reduced stress and burnout and increased job satisfaction in employees as a result (distal outcomes for employees)• If managers experience senior management support, then they will engage in more self-care activities (intermediate outcome) and as a result, managers will report improvements in wellbeing, stress, and burnout (distal outcomes for managers)• If managers experience supportive senior managers, they will engage in more transfer attempts and as a result they will report larger improvements in staff-care (intermediate outcome), which will result in lower levels of stress and burnout and increased job satisfaction among employees (distal outcomes).• Managers, who experience the training as relevant and addressing the challenges in their everyday work, will have more transfer attempts, and as a result they will increase staff-care (intermediate outcome), which will result in larger improvements in psychosocial work environment outcomes (intermediate outcome) leading to improvements in health and satisfaction outcomes of employees (distal outcomes).• Managers, who experience a higher degree of intention to transfer, will have not only more, but also more diversified and repeated transfer attempts (proximal outcome), and as a result more both self-care and staff-care behaviors (proximal outcome) leading to employees reporting higher levels of both self-care and perceived staff-care (proximal outcomes in employees).• Managers, who experience staff shortage, will have fewer opportunities for transfer due to work pressure, and thus less transfer attempts, and as a result they will likely not increase their staff-care behavior (intermediate outcome) leading to a lack of improvement in stress, burnout and job satisfaction among employees (distal outcome in employees).

The purpose of these CMO’s is to obtain in-depth knowledge on what works for whom (e.g. how support from senior management is experienced or how they formulate their own needs in their daily practice) under which circumstances.

#### Quantitative process evaluation

A quantitative process evaluation will be conducted throughout the study during assessments at baseline, 1^st^ follow-up and 2^nd^ follow-up. In addition, all participating managers in the intervention group will be asked to answer a short survey following each module to assess their experience of the training.

Contextual factors that will be addressed are turnover in the hospital wards, span of control, and the support of senior management and subordinates of initiatives related to well-being and the psychosocial work environment. Other factors are time, resources, and opportunities to practice what is learned during the training and in the daily work setting of the managers. Cognitive, emotional, and behavioral aspects known to be influential of transfer will also be addressed such as perceptions of how the training and content fits the daily work of managers and various transfer elements such as confidence, intention, and motivation to transfer, acceptability of the training and experience of integrity of the training will also be assessed. Please see specifications below.

##### Quantitative process measures

To estimate the central aspects that relate to training transfer, selected items from the Generalized learning transfer system inventory will be employed [52]:

Readiness for change will be assessed with: *“Before the training I had a good understanding of how it would fit my job-related development”.* The item is answered on a five-point Likert scale ranging from strongly disagree (1) to strongly agree (5).

Motivation to transfer will be assessed with: *“I get excited when I think about trying to use my new learning on my job.* The item is answered on a five-point Likert scale ranging from strongly disagree (1) to strongly agree (5).

Time pressure as a contextual factor is assessed with: *“My workload allows me time to try the new things I have learned”.* The item is answered on a five-point Likert scale ranging from strongly disagree (1) to strongly agree (5).

To assess whether new knowledge was acquired after each module the following item from the Questionnaire for Professional Training Evaluation [53] will be used after each module: *“ I know substantially more about the training contents than before”.* The item is answered on a five-point Likert scale ranging from strongly disagree (1) to strongly agree (5).

Fit of training content to the job will be assessed with three items: *“The activities and exercises the consultant(s) used helped me know how to apply my learning on the job”*, *“It is clear to me that the people conducting the training understand how I will use what I learn”, and “ The way the consultant(s) taught the material made me feel more confident I could apply it”.* All Items are answered on a five-point Likert scale ranging from strongly disagree (1) to strongly agree (5).

Intention to transfer [54] will be assessed after each module with the items: “*I believe what I learned on the training can help me at work*”, “*The skills I developed during the training will help me at work”, “I developed new skills for my work that I didn't have before*”. Both items are answered on a five-point Likert scale ranging from strongly disagree (1) to strongly agree (5).

To assess whether the participants experience sufficient opportunities to apply learned knowledge and skills, the following items by Holton [55] will be used after module 2 to 5 as well as in the 1^st^ and 2^nd^ follow-up: “*I have had the tasks necessary to apply the skills and knowledge I learned on the training*”,”*I have the necessary resources to use what I learned in training*”, and “*I have the information necessary to apply the skills and knowledge I learned on the training course*”. All Items are answered on a five-point Likert scale ranging from strongly disagree (1) to strongly agree (5).

To assess whether transfer was successful the following item from the Questionnaire for Professional Training Evaluation [53] will be applied during 1^st^ and 2^nd^ follow-up: “*In my everyday work, I often use the knowledge I gained in the training*”, “*I successfully manage to apply the training content in my everyday work*”, "*I am able to transfer the skills learned in training courses back to my actual job*”. Items are rated on an 11-point scale ranging from 0 (Therefore, an 11-point response scale ranging from 0 percent (completely disagree) to 100 percent (completely agree).

To assess the integrity and climate of the training, we will also ask the participants the following questions (also used by Vuori et al. [56]) during first follow-up: “*Did the consultant(s) make you feel like your participation was valued?*”, “*Did the consultant(s) do or say something that makes you think they understand your situation?*”, “*Did the consultant(s) encourage you to participate in the assignments they gave*”, “*Did you find the atmosphere friendly and encouraging*?”, “*Did you find group discussions useful?*”, “*Did you share your own experiences in the group*?”.

Support from senior management and colleagues will be measured with items already mentioned among the outcome measures previously described in this paper.

##### Analyses related to the process evaluation

Analyses of quantitative process data will be conducted through descriptive statistics and methods of investigating predictors of outcome change for example by adding process variables to quantitative models to investigate whether the variable was related to specific outcomes. The results of the effect evaluation, and the quantitative and qualitative process evaluation will be integrated to gain the highest level of insight into answering CMO’s listed above.

#### Qualitative process evaluation

Barriers and facilitators of adherence and transfer of training to daily practices will be explored through semi-structured interviews with the managers receiving training, their employees and other stakeholders such as the clinical directors. Participant observation of the training modules will also be conducted.

##### Interview data

Interviews will be conducted in order to gain in-depth understanding of the different parts of the leadership training and between module exercises [57], including how they influence each other as well as how the training is transferred to the daily practices and setting of the managers. The interviews will be conducted at different time points during the 5 months of the training and throughout the follow-up period. Individual interviews will be conducted with 14 randomly selected managers after Module 3 has been completed. Focus group interviews will be conducted with in total 10–15 participating managers at the end of Module 5. In addition, selected managers from each group will be interviewed five to six months after completion of the leadership training. Interviews are also conducted with 1–2 managers focusing on the experiences with group exercises, both between Modules 2 and 3, and between Modules 4 and 5. In addition, focus group interviews are conducted with 3–4 employees from 3 selected departments (from which managers participate in the training modules) after the training. The employee interviews are conducted as focus groups, as this interview format allows participants to discuss and nuance each other's views [58].

A semi-structured interview guide is prepared, i.e. the questions are developed and expanded as the modules and group exercises are completed. In this way, the benefits and possible challenges for the managers can be continuously identified and used to further explore and develop the configurations of the CMOs. The focus will be on the participants' own perspectives, partly on their own challenges in dealing with the psychosocial work environment, partly on their own well-being and health, and partly on their perception of what the context means for their challenges and their attempts to transfer their learning from the training. Examples of questions from the semi-structured interview guide could be: Can you describe your own motivation or reasons for signing up to the Matterhorn-training program? How do you believe that the training program can help you to improve your psychosocial management in the department? How does the form of the training, and the different formats, fit your own preferred way of learning – can you use it, in daily practice? How, in your view, has the employees benefitted from your participation in the training program? In the focus group interviews, these issues can be discussed between the participants, and they can respond to each other's experiences. The individual interviews are intended to allow reflection on own practice and the context it is part of. In relation to transfer, the interviews after the final modules will focus on what improvements, if any, the participants experience and how these improvements have influenced their ability to manage well-being and the psychological working environment in their wards. Furthermore, which factors they believe have contributed positively to implementation and transfer of the leadership training, as well as the issues that may pose a potential barrier and need to be addressed for the training to have the desired impact.

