## Methods

### Study design and participants

The project will investigate the effects of training frontline managers in hospitals in the Central Denmark Region through a cluster randomized waitlist controlled trial. The project aims to include 200 managers who, after registration and informed consent for the research project, are randomly allocated to receive either leadership training commencing in the beginning of 2023 (intervention group), or leadership training commencing in the beginning of 2024 (waitlist control group). Recruitment began in May 2022 and ended during January 2023. The participating managers are randomized by hospital ward, but the vast majority of wards include only one participating manager. Because some managers are clustered in wards, the wards are stratified into three groups of wards with: 1. One participating manager in the ward, 2. two participating managers, and 3. three or four participating managers. In each strata, wards are randomly assigned to equal sized intervention and control groups. For each strata, we randomly number all wards and using the RAND function in Excel, each ward is assigned with a random number between 0 and 1. The lowest 50% of numbers are assigned to the intervention group and the other 50% are assigned to the control group. In addition, the intervention group is randomly assigned to five training groups. The randomization is conducted by a neutral research assistant. All managers and their employees will be invited to complete outcome questionnaires at baseline prior to training, as well as 6-months and 12-months post baseline. An overview is presented in the flowchart in Fig. 1. Managers will also receive a short questionnaire related to the process evaluation following completion of each training module to assess the learning experience (see further description of the process evaluation below).

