### The intervention

The leadership training consists of five full-day training modules over five months from the beginning of the training delivered to groups of up to 20 participants. There will be additional meetings in smaller practice groups between each module to solidify content learned in the training modules.

The training modules are facilitated by two experienced Human Resource Development (HRD) consultants, employed in Corporate HRD in the Central Denmark Region and with expertise in organizational psychology and leadership development within the region. Short video presentations of research-based knowledge will be provided during the modules by researchers with expert knowledge in subjects relevant for the training.

The training group meetings between the modules will focus on transferring the learning from each module into the managers' daily working context. The first of the meetings will be facilitated by an HRD consultant to support a meeting structure and the psychological safety in the group and the training. The next three meetings will be conducted by the group itself.

During the waiting period, the control group will have the opportunity to participate in a meeting with introductory information on the project and the psychosocial work environment.

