### Data collection (effect evaluation)

The participating managers randomly allocated to the intervention and waitlist control group and all their employees, will be invited to complete questionnaires at baseline, 6 months follow-up and 6-months post training (12 months follow-up). Register data on sickness absence and staff turnover will be retrieved for the one year period prior to and following baseline for all managers and employees. In addition, a process evaluation will be conducted including both quantitative and qualitative data (see description below).

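### Late interviews of selected intervention-arm managers fall just before, or overlap, the 12-month questionnaire and could shift self-reported manager outcomes in one arm only

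*Protocol article*

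**What the plan says.** The Interview data section schedules several rounds of interviews. In the last round, "selected managers from each group will be interviewed five to six months after completion of the leadership training". The same section says that interviews after the final modules ask "what improvements, if any, the participants experience and how these improvements have influenced their ability to manage well-being". It also covers managers' own challenges, their own well-being and health, and the factors that helped or hindered transfer. Individual interviews are described as an occasion to reflect on one's own practice.

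The Qualitative process evaluation section limits interviews to "semi-structured interviews with the managers receiving training, their employees and other stakeholders such as the clinical directors". Under Study design and participants, "the intervention group is randomly assigned to five training groups", and the waitlist arm begins its training at the start of 2024.

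On timing, The intervention section describes "five full-day training modules over five months from the beginning of the training". Data collection (effect evaluation) describes the last questionnaire as "6-months post training (12 months follow-up". The article does not say whether a late interview comes before or after that manager's 12-month questionnaire, how many managers are selected for this round, or how interviewed managers are treated in the effect analysis.

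**The concern.** Apart from register-based sickness absence, the primary outcomes for managers (self-care, staff-care, stress, burnout, job satisfaction) are self-reported by people who know their arm. Blinding the data analyst does not protect against a change in how managers rate themselves.

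The interview covers the ground that the questionnaire then scores. By the article's own account it also resembles the training: the Background reports that reflective elements appear most effective, and every module includes reflection. An interview about one's own practice shortly before the 12-month ratings is therefore an extra prompt that trained managers can receive and controls cannot. Any resulting shift would be counted as an effect of training in the baseline-to-12-month contrast. It would also enter the 6-to-12-month contrast, since the late interviews fall within that interval. A late prompt there could be mistaken for maintenance, or loss, of effect.

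**Working it through.** **1. When the interviews fall.** The article supports two anchors for the end of training, counted from baseline.
- Data collection (effect evaluation) equates 12 months of follow-up with six months after training, so training ends at about month 6. Interviews: 6 + 5 = 11 to 6 + 6 = 12, that is, months 11 to 12.
- The intervention section gives five months of training. If it starts at baseline, training ends at month 5. Interviews: 5 + 5 = 10 to 5 + 6 = 11, that is, months 10 to 11.

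On both readings the window ends at or before month 12. Collecting the data leaves the questionnaire open for at least three weeks, so interviews and responses can also overlap. The order for an individual manager is not stated.

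**2. Which arm.** The interviewees are managers who have received training, and the five training groups all lie in the intervention arm. Controls start training in 2024, so none can be five to six months past training before the 12-month questionnaire. Controls are offered an introductory meeting, activities and regular communication. No interview is described for them.

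**3. The plan's own power figure.** Sample size gives an effect of 0.54, baseline correlation 0.5, group size 20, intra-group correlation 0.02, 80 followed per arm and alpha 0.05 (taken as two-sided).
- Design effect = 1 + 19 × 0.02 = 1.38.
- Change-score variance factor = 2 × (1 − 0.5) = 1.
- SE = √(1.38 × 2/80) = 0.186.
- Power = Φ(0.54/0.186 − 1.96) = 0.828, which agrees with the stated 0.83.

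**4. Possible size of the shift.** With k managers interviewed and a shift of s SD in each, the arm mean moves by b = (k/80) × s. The article gives neither k nor s for this round, so both are assumptions. The range k = 10 to 15 is of the same order as the manager interview counts that are stated (14 individual interviews after Module 3; 10–15 in focus groups after Module 5).
- k = 10, s = 0.2: b = 0.025 SD, and 0.025/0.54 = 4.6% of the planned effect.
- k = 10, s = 0.3, or k = 15, s = 0.2: b = 0.0375 SD, 6.9%.
- k = 15, s = 0.3: b = 0.056 SD, 10.4%.

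**5. Effect on false positives.** If training truly had no effect, the two-sided error would be 1 − Φ(1.96 − b/SE) + Φ(−1.96 − b/SE). With the SE above this gives 0.052 at b = 0.025 and 0.061 at b = 0.056, against a nominal 0.05.

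**6. What is not touched.** Sickness absence and turnover come from registers. The 6-month questionnaire precedes the late interviews, so the baseline-to-6-month contrast is free of them. Employee focus groups take 3–4 people from three departments. That is 9 to 12 people if the number is per department, out of roughly 2,500 intervention-arm employees (half of 5,000): 9/2,500 = 0.36% to 12/2,500 = 0.48%.

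**The case against.** The strongest reply has four parts.

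- **Scheduling.** The order of interview and questionnaire is not stated, and a journal article may leave such detail to the full protocol. This stands in part. The order is indeed unstated, but the article itself fixes the interview window, and that window ends at or before the questionnaire.
- **Direction.** The guide asks about improvements only if there are any, and also about challenges and barriers. Reflecting on strain could lower self-ratings. This stands: a reader might infer that the interviews inflate the training effect, and the article does not support that. A downward shift would still be an artefact confined to one arm.
- **Size.** Only selected managers are interviewed. A reader could reach a large figure by assuming 20 interviewees and 0.5 SD each, since 20/80 × 0.5 = 0.125 SD, or 23% of 0.54. That needs more managers than any round of manager interviews states, and it credits one conversation with nearly the whole effect planned for a five-month programme. It is not a reasonable estimate.
- **Other prompts.** Intervention managers are surveyed after every module, and transfer questions are part of both follow-up assessments. They are prompted anyway, so the added influence of an interview is smaller still. This stands as a limit on size. It does not justify adding a further avoidable prompt.

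A reader might also place confidence among the primary outcomes at risk. It is a registered secondary outcome.

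**Conclusion.** The point holds as a minor, avoidable asymmetry. Selected trained managers can be interviewed about their practice and perceived gains in the one to two months before the 12-month questionnaire, or while it is open, with no control counterpart. Their self-ratings at that time could shift in either direction.

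A plausible movement in the arm mean is about 0.03 to 0.06 SD. This rests on two assumptions that the article neither states nor excludes: 10 to 15 of 80 managers interviewed, and 0.2 to 0.3 SD each. A reader might conclude that the 12-month comparison is invalid. The documents do not support that: the exposed group is a subset, the effect is diluted across the arm, and the outcomes listed in step 6 of the working lie outside its reach.

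**What to change.** State in the protocol that each late interview takes place only after that manager has submitted the 12-month questionnaire or its response window has closed. Reminders already go only to those who have not responded, so completion is known for each manager and the rule can be applied without new systems. Where practical, hold the focus groups planned for the end of Module 5 after the 6-month questionnaire in the same way.

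The cost is a delay of some weeks and slightly longer recall in the interviews. No extra staff, interviews or participants are needed.

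Do not rely on dropping interviewed managers from the analysis. The Module 3 interviewees are chosen at random, but the late ones are described only as selected. Removing them from one arm, with no matching removal among controls, can itself introduce selection bias. If some late interviews do come first, record which managers were affected and report an analysis without them only as a clearly labelled sensitivity check.
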